Study type	Allocation: non-randomized Intervention model: parallel assignment Primary purpose: treatment
Date of first enrollment	December, 2024.
Target sample size	36
Recruitment status	Recruiting.
Primary outcome(s)	Method of measurement: Biopotentials (ECG, PCG, EDA, fNIRS, respiratory rhythm) Timepoint: pre-treatment, post-treatment, and follow-up.
Key secondary outcomes	Changes in neuroimaging measures Timepoint: pre-treatment, post-treatment, and follow-up. Changes in biopotential measures Timepoint: pre-treatment, post-treatment, and follow-up.
Ethics Review	This project received ethical approval from Harran University with the decision of the clinical research ethics committee on 03 July 2024.
Completion Date	October, 2025

The SPIRIT reporting guidelines recommend these items to be included in trial protocols to provide a brief, structured overview of a trial.

Our study is a non-randomized, parallel-group cohort study. Patients were assigned to a group in the chronological order of enrollment in the study. Therefore, consecutive sampling was used for allocation concealment. The inclusion and exclusion criteria will be applied uniformly to all patients, regardless of group, without exception. At inclusion, baseline characteristics will be compared between groups, including age, sex, and whether participants experienced the earthquake as a traumatic event. The comparability of the groups at inclusion will be verified by ensuring that there are no significant differences between groups.

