#### Inclusion criteria

3.1.1

Young earthquake survivors without specific diseases who recently experienced the earthquake in our region in February 2023 will be selected. The sample sizes of 20–25 participants have been selected in similar studies (Maheu et al., 2005; Nakajima et al., 2016; Tegeler et al., 2023; Zabrecky et al., 2020). The sample size selected (*n* = 10–12 participants per group) follows the rule of thumb proposed by Julious (2005), which is widely recognized in the methodological literature as a minimum standard for pilot studies (Julious, 2005). Furthermore, our proposal will use deep learning and current artificial intelligence algorithms. Because data can be obtained from each measurement within the time-series dataset used for this purpose, a substantial amount of data can be generated through windowing and data augmentation, and transfer learning can be performed; it is assumed that a dataset from 36 participants will be sufficient. Consequently, at least 30 university students aged between 20 and 25 years who experienced and survived the earthquake will take part in the experiment. They must have experienced the earthquake as a significant and severe event. In accordance with the inclusion criteria, the participants will be healthy, non-obese men (*n* = 18) and women (*n* = 18). In particular, all participants should have experienced the earthquake disaster in the local region. All participants must be free of any chronic or acute infection, neurological, psychiatric, and/or cardiovascular disease. They must be non-smokers, have no alcohol or drug addiction, and not be under any medical treatment. Pregnant or breastfeeding women will not be included in the study.

University students who survived the earthquake in the region will be invited to volunteer for this study. The inclusion and exclusion criteria will be verified by interviewing the volunteers. Participants will then undergo a medical examination by a psychiatrist. If no problems are found, participants will be recruited for the study.

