#### Study design

3.1.2

An intervention and control group will be formed with 20 and 10 participants, respectively. The intervention and control groups will be exposed to the same mental stress.

*Control group:* 10 young healthy earthquake survivors will not receive any auditory stimulation.

Intervention group: 10 young healthy earthquake survivors will be subjected to closed-loop, real-time heart sound (PCG) stimulation to create biofeedback.Intervention group: 10 young healthy earthquake survivors will be given an auditory stimulus of their heart sound and a metronome synchronized with their mean heart rate (MHR) recorded during a calm state.

Participants will be taken individually to the experimental room and seated comfortably in a quiet and spacious environment. Before the first session, a scientific introduction, the purpose of the study, an explanation of how it will be conducted, an explanation of the mental stress to be induced, and basic information about the measurements to be taken will be provided at the information meeting (using an introduction video). The participant should feel as comfortable as possible, and no additional sources of stress should be created. Participants will be instructed to breathe normally and avoid moving their legs.

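### Non-significant baseline tests cannot verify that non-randomised groups of 10 to 12 are comparable

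*Protocol article*

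**What the plan says.** The Methods/design section is explicit about allocation: "Our study is a non-randomized, parallel-group cohort study", and "Patients were assigned to a group in the chronological order of enrollment in the study". It then plans a baseline comparison in which "baseline characteristics will be compared between groups, including age, sex, and whether participants experienced the earthquake as a traumatic event", and gives the rule for reading it: "The comparability of the groups at inclusion will be verified by ensuring that there are no significant differences between groups".

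Group size appears in two places. Inclusion criteria (3.1.1) gives "10–12 participants per group) follows the rule of thumb" for pilot studies. Study design (3.1.2) says "An intervention and control group will be formed with 20 and 10 participants, respectively", with the 20 split into two arms of 10. Table 1 gives a target of 36, which is 12 per arm if split equally over three arms.

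Statistical methods (3.5.1) compares RMSSD, HF and LF at the final session with the first session. The model is either a linear mixed model with group and time as fixed effects or an ANCOVA whose covariates are not named. The article states no significance level for the baseline tests, no margin for an acceptable imbalance, and no adjustment for sex or enrolment date.

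**The concern.** The rule treats failure to reject a null hypothesis as proof that the null holds. That is an error at any sample size, and at 10 to 12 per group it has practical consequences, because the tests have little power against imbalances large enough to matter.

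In a randomised trial such tests would be merely redundant. Here no random assignment stands behind the groups, so systematic differences are possible. Assignment followed enrolment order, data collection ran from December 2024 to 30 June 2025 (Methods/design), and the Limitations section accepts that season affects physiological parameters. If arms tended to fill at different times, group and calendar time are mixed. A test of age, sex and trauma experience would not show it.

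At stake are the effect-size and variance estimates that Statistical methods intends for planning a confirmatory trial. If the arms are declared comparable on this rule, readers will take those estimates as free of baseline confounding when the check could not have shown it.

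**Working it through.** **Inputs.** n per group = 10 (Study design) or 12 (36/3, Table 1; upper end of the range in Inclusion criteria). Alpha = 0.05 two-sided is an assumption, since none is stated. The size of imbalance is also an assumption, shown from 0.3 to 1.0 SD. The plan has no power figure to reproduce: its group size comes from a pilot rule of thumb. The totals do agree arithmetically: 3 × 10 = 30 and 3 × 12 = 36.

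**Step 1: smallest observed gap that would be flagged.** In SD units this is t(0.975; 2n − 2) × √(2/n).
- n = 10: 2.101 × √0.2 = 0.94 SD.
- n = 12: 2.074 × √(1/6) = 0.85 SD.

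Any smaller observed difference between two arms passes as comparable.

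**Step 2: chance that a true imbalance d is flagged.** Noncentral t with 2n − 2 degrees of freedom and noncentrality d × √(n/2). At d = 0.5 the noncentrality is 1.12 (n = 10) or 1.22 (n = 12).

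| True imbalance | n = 10 | n = 12 |
|---|---|---|
| 0.3 SD | 10% | 11% |
| 0.5 SD | 19% | 22% |
| 0.8 SD | 40% | 47% |
| 1.0 SD | 56% | 65% |

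A single three-group ANOVA does no better at the moderate size. Depending on how the means are arranged, it gives 14–18% (n = 10) or 17–21% (n = 12) at 0.5 SD, and 31–40% or 37–48% at 0.8 SD. For 80% power the true imbalance would have to be 1.32 SD (n = 10) or 1.20 SD (n = 12). Conversely, 80% power at 0.5 SD needs about 63 per arm, and at 0.8 SD about 25 (normal approximation).

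**Step 3: sex, by Fisher's exact test.**
- Observed 7/10 v 3/10: p = 0.18. Observed 8/12 v 4/12: p = 0.22. Both would pass.
- With true shares of 30% and 70%, power is 24% (n = 10) or 39% (n = 12). Over 35/65 to 25/75 it ranges from 12% to 42% and from 21% to 61%.

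**Step 4: what adjusting for enrolment date would cost.** The article does not say whether enrolment order rotated through the arms or filled them one after another. Suppose three consecutive blocks with evenly spaced enrolment (assumed) and a linear date term. The within-arm sum of squares of date is 3 × n(n² − 1)/12 = n(n² − 1)/4. The variance of a contrast between arms whose mean dates differ by Δ is multiplied by 1 + Δ²n/(2 × that sum).
- Adjacent arms, Δ = n: 1 + 2n²/(n² − 1) = 3.02 (n = 10) or 3.01 (n = 12).
- First v last arm, Δ = 2n: 1 + 8n²/(n² − 1) = 9.08 or 9.06.

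The standard error is therefore multiplied by about 1.7 or 3.0. Under strict rotation the cost is essentially nil.

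**The case against.** The best defence is that the baseline check does not stand alone. Eligibility is applied uniformly and is narrow: healthy, non-obese, non-smoking students aged 20–25, with 18 men and 18 women overall. Time of day is fixed, menstrual onset is recorded, and the Limitations section aims to keep most recordings within one season. The primary comparison uses each participant's first-session value. The study is also labelled preliminary. All of this stands, and it limits the damage. It does not make the rule sound: narrow eligibility does not balance arms, and neither stated model names sex or calendar time.

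Some stronger readings do not hold:
- **The check is the only safeguard, or would almost always pass.** The measures above rule out the first. On the second, a true 1.0 SD gap would be flagged more often than not.
- **A baseline gap would pass into the result as a bias of a given size.** That presumes a final-session comparison that ignores the first session, which the plan does not propose.
- **Baseline HRV and DASS-21 are wrongly left out.** The list is introduced as non-exhaustive, and a journal article need not give the full baseline table.
- **The trauma item cannot vary.** Entry requires that "They must have experienced the earthquake as a significant and severe event", so it may vary little. But the two wordings differ, and the article does not say how either is measured.
- **The wording invites exclusion or reassignment to obtain balance.** Nothing in the article permits this. The verb is loose, no more.

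**Conclusion.** The point holds. The article fixes a decision rule that would support a false conclusion: at 10 to 12 per group, a moderate imbalance (0.5 SD) goes unflagged about four times in five, and a large one (0.8 SD) somewhat more than half the time. The figures rest on an assumed two-sided 5% level and on the assumed imbalance sizes, but from 0.3 to 0.8 SD the test misses more often than it detects. The rule is stated outright, so it is not a detail left to an analysis plan.

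The finding concerns what non-significance is taken to show. It does not establish that the arms are in fact unbalanced or that the primary estimate is biased by a known amount. Confounding with calendar time is possible but unproven, because the mapping from enrolment order to arm is not given.

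**What to change.** 1. Delete the claim that comparability is verified by non-significance.
2. Report standardised differences by arm, without significance tests, for the baseline variables already collected, including RMSSD, HF, LF, DASS-21, sex and enrolment date.
3. Adjust the primary model for the baseline outcome and sex, whatever balance is observed.
4. Report how enrolment order mapped to arms. If assignment rotated, adjust for enrolment date as well. If arms were filled in blocks, do not force date into the primary model, given the variance cost in Step 4. Show it as a sensitivity analysis and state the confounding with calendar time as a limitation.

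The cost is wording plus one or two degrees of freedom (sex, and date if assignment rotated). No new data are needed, so the change remains possible although collection has finished.

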In order to carry out this study, the following basic measurements—sex, age, height, weight, blood pressure, etc.—and relative measurements derived from the basic measurements will be extracted. In this context, the cardiovascular, emotional, and psychological states of earthquake survivors will be observed through biomedical signals. Electrocardiography (ECG), respiratory rhythm, and electrodermal activity will be measured to evaluate the autonomic nervous system, particularly the parasympathetic nervous system. A metronome based on the heart rate derived from the ECG and the measured phonocardiogram signal will be used for auditory stimulation. Our protocol will calculate and use the biological markers of heart rate variability (HRV), including low-frequency band (LF), high-frequency band (HF), LF/HF, standard deviation of NN intervals (SDNN), and root mean square of successive differences (RMSSD). The fNIRS device will measure changes in oxygenated and deoxygenated hemoglobin concentrations in the cortical brain structure before and during mental exertion. The sound of a heartbeat will be evaluated to determine its effects on fNIRS results in the prefrontal cortex during relaxation and stress.

Each participant will have 390 min of experimental activity, including 330 min of measurements.

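### Non-significant baseline tests with 10 to 12 per arm cannot verify that the non-randomised arms are comparable

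*Protocol article*

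**What the plan says.** Methods/design describes the design as follows: "Our study is a non-randomized, parallel-group cohort study". On allocation it says: "Patients were assigned to a group in the chronological order of enrollment in the study". On the check at entry: "At inclusion, baseline characteristics will be compared between groups, including age, sex, and whether participants experienced the earthquake as a traumatic event". The next sentence gives the decision rule: "The comparability of the groups at inclusion will be verified by ensuring that there are no significant differences between groups". No test, significance level, margin or limit on a standardised difference goes with it.

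Inclusion criteria (3.1.1) gives the group size as "10–12 participants per group". Study design (3.1.2) has "An intervention and control group will be formed with 20 and 10 participants, respectively", with the 20 split into two arms of 10. Table 1 gives a target of 36, which is 12 per arm if the arms are equal.

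Statistical methods (3.5.1) names RMSSD, HF and LF as the primary pilot outcomes. The final session is compared with the first, by a linear mixed model with group and time as fixed effects or by ANCOVA. No covariate is named.

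**The concern.** The rule reads a failure to find a difference as a finding of no difference. In a randomised trial a poor baseline test is mostly harmless, because the allocation already makes the arms alike in expectation. Here the arms are filled by order of enrolment, so real differences at entry are possible. The article does not say whether consecutive participants rotate through the arms or fill one arm after another. In the second case calendar time would differ systematically between arms. Recruitment ran from December 2024 to the end of June 2025, and Limitations accepts that season affects physiological measurements.

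At stake is what the report may claim. A passed check would let it call the arms comparable on evidence that cannot show this. The effect sizes for RMSSD, HF and LF are meant to size a confirmatory trial, so readers may give them more weight than the design allows.

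**Working it through.** The article gives no figure for this check, so there is none to reproduce. The one consistency check is that 30 / 3 = 10 and 36 / 3 = 12, which matches the stated range per group.

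**Inputs.** n = 10 or 12 per arm (3.1.1, 3.1.2, Table 1). Assumption: two-sided alpha 0.05 and a two-sample t-test, since neither is stated.

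**1. Largest observed difference that still passes.** d = t(0.975, 2n − 2) × √(2/n).
- n = 10: 2.101 × 0.447 = 0.94 SD
- n = 12: 2.074 × 0.408 = 0.85 SD

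**2. Chance that a true imbalance is missed.** Non-central t with 2n − 2 degrees of freedom and non-centrality d × √(n/2). For d = 0.5 this is 0.5 × √5 = 1.118 at n = 10 and 0.5 × √6 = 1.225 at n = 12.

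| True imbalance | Flagged, n = 10 | Missed, n = 10 | Flagged, n = 12 | Missed, n = 12 |
|---|---|---|---|---|
| 0.25 SD | 8% | 92% | 9% | 91% |
| 0.5 SD | 18% | 82% | 22% | 78% |
| 0.8 SD | 40% | 61% | 47% | 53% |
| 1.0 SD | 56% | 44% | 65% | 35% |

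(Unrounded flag rates: 0.185 and 0.216 at 0.5 SD; 0.395 and 0.466 at 0.8 SD. Rounding makes one row add to 101%.)

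**3. Sensitivity to the assumed test** (largest passing difference, n = 10 / n = 12).
- Alpha 0.10: 0.78 / 0.70 SD
- Bonferroni for three pairs: 1.18 / 1.06 SD
- Three-arm F-test, one arm differing from the other two: 1.00 / 0.91 SD

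The three-arm F-test flags a single arm shifted by a true 0.5 SD in 18% / 21% of cases. No variant makes the rule informative.

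**4. A binary variable such as sex** (Fisher exact test). These splits would pass:
- 8 of 10 men against 3 of 10: p = 0.07
- 9 of 12 against 4 of 12: p = 0.10

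**5. Sample size at which the test would be informative.** For 80% power to flag a true 0.5 SD imbalance: 2 × (1.960 + 0.842)² / 0.5² = 62.8, so 63 per arm, about five to six times the planned size.

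**The case against.** The strongest reply is that the check is not what protects the primary result. The planned comparison is final session against first session, by mixed model or ANCOVA, so each participant's own starting value of RMSSD, HF or LF enters the analysis. Eligibility is uniform and narrow, and Limitations promises an effort to record within one season. The check gates nothing: no analysis, covariate or exclusion depends on it. The study calls itself preliminary.

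Much of this stands, and it rules out several stronger readings.

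- A reader might infer that the test is the only safeguard. It is the only stated check of comparability, but the safeguards above exist beside it.
- A reader might infer that any imbalance at entry passes straight into the primary contrast. A difference in the outcome's own starting value would not do so in full under either model. What remains is confounding by factors that affect change, such as sex or time of enrolment.
- A reader might infer that the check will almost always pass. The table does not support that: a 0.8 SD imbalance is flagged in 40% to 47% of cases. With three independent tests at 5% and no true difference, at least one is significant with probability 1 − 0.95³ = 14%.
- A reader might infer that the primary outcomes, blood pressure or DASÖ-21 are left out of the baseline comparison. The list of variables is open-ended, the article says that "height, weight, blood pressure" and other basic measurements are recorded, and a condensed article need not print the full baseline table.

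The reply does not rescue the rule itself. The model is left as a choice between two, no covariate is named, and the article still says that comparability will be verified by a method that cannot verify it.

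**Conclusion.** The concern holds as a fault in a stated rule. Assuming a two-sided 5% t-test, observed differences just under 0.94 SD (10 per arm) or 0.85 SD (12 per arm) count as comparable, and a true 0.5 SD imbalance goes unflagged in 78% to 82% of cases. Other reasonable tests put the passing limit between about 0.7 and 1.2 SD, and the conclusion does not change.

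The consequence is an unsupported claim in the report, with residual confounding from chronological assignment left unacknowledged. The documents do not show that the primary analysis is invalid. The point should be fixed but is not critical, because the study is a pilot, the planned model gives partial protection, and no stated analysis turns on the result of the check.

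**What to change.** 1. In Methods/design, delete the significance rule and the claim that comparability is verified.
2. Report standardised differences between arms with 95% confidence intervals for the recorded baseline variables, including pre-treatment (first-session) RMSSD, HF and LF, blood pressure, DASÖ-21, age, sex and enrolment date. Enrolment date matters most under assignment by order of entry.
3. In Statistical methods, commit to adjusting the primary comparison for the pre-treatment value of the outcome, whatever the baseline p-values. This is the ANCOVA option already offered. State which recording supplies that value, and that it precedes any sound stimulus.
4. State that residual confounding from sequential, non-randomised assignment cannot be excluded.

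The cost is a text change and one covariate that is already recorded. No new data are needed, so the change is possible although the article gives data collection as complete by 30 June 2025. The one loss is the claim of verified comparability, which the data could not have supported.

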### Protocol and procedure

3.1

#### Inclusion criteria

3.1.1

Young earthquake survivors without specific diseases who recently experienced the earthquake in our region in February 2023 will be selected. The sample sizes of 20–25 participants have been selected in similar studies (Maheu et al., 2005; Nakajima et al., 2016; Tegeler et al., 2023; Zabrecky et al., 2020). The sample size selected (*n* = 10–12 participants per group) follows the rule of thumb proposed by Julious (2005), which is widely recognized in the methodological literature as a minimum standard for pilot studies (Julious, 2005). Furthermore, our proposal will use deep learning and current artificial intelligence algorithms. Because data can be obtained from each measurement within the time-series dataset used for this purpose, a substantial amount of data can be generated through windowing and data augmentation, and transfer learning can be performed; it is assumed that a dataset from 36 participants will be sufficient. Consequently, at least 30 university students aged between 20 and 25 years who experienced and survived the earthquake will take part in the experiment. They must have experienced the earthquake as a significant and severe event. In accordance with the inclusion criteria, the participants will be healthy, non-obese men (*n* = 18) and women (*n* = 18). In particular, all participants should have experienced the earthquake disaster in the local region. All participants must be free of any chronic or acute infection, neurological, psychiatric, and/or cardiovascular disease. They must be non-smokers, have no alcohol or drug addiction, and not be under any medical treatment. Pregnant or breastfeeding women will not be included in the study.

University students who survived the earthquake in the region will be invited to volunteer for this study. The inclusion and exclusion criteria will be verified by interviewing the volunteers. Participants will then undergo a medical examination by a psychiatrist. If no problems are found, participants will be recruited for the study.

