#### ECG, EDR, and fNIRS data

3.4.2

The data obtained using deep learning techniques will be classified. Classification studies will be performed with deep learning to emphasize to characterize differences between the control and treatment groups, as well as differences before and after treatment within groups and to show that the difference is significant. The data will be converted into spectrogram images and processed as time-series data. A suitable pretrained network (AlexNet, SqueezeNet, GoogLeNet, etc.) will be used with transfer learning, and classification will be performed. Technical information is provided in our published articles (Özcan and Alkan, 2021, 2023a, 2023b).

On the other hand, correlation analysis will be performed using deep learning method (Alessandrini et al., 2023). Then, the features used in the classification will be evaluated using explainable artificial intelligence techniques.

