Transfer learning will provide faster and more effective learning algorithms by reducing the size of the dataset. The network will be fine-tuned with transfer learning, and feature extraction will be performed quickly. The dataset will be expanded using smaller time windows of the signals. If we divide 330 min of recordings into 10-s segments, 1980 time series or representative images will be processed for each measurement. In addition, the dataset can be expanded using the data augmentation technique. Data from 36 subjects would be sufficient in this case. Of the dataset, 70% will be used for training the neural network, 15% for validation, and 15% for testing. To ensure that the training and test sets are created on an individual basis, we would need a larger number of participants. This could be the subject of future studies.

Despite their excellent performance, deep learning models produce good results without being able to explain why. These models act as a black box for users. This is one of the main limitations of deep learning in medicine. Therefore, the issue of the explainability of neural networks has emerged (Ilias and Askounis, 2022; Ong et al., 2021; Thibeau-Sutre et al., 2023). The behavior and reasons for the importance of features automatically used in artificial intelligence tools will thus be understood (Ong et al., 2021). The XAI framework will use different techniques, such as LIME (Local Interpretable Model-agnostic Explanations), Occlusion Sensitivity, and Grad-CAM. These methods, each with a specific approach to classifying an image, produce a map showing the regions of the image that are important for the process. The network will use these maps for decision-making.

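### Calling 36 participants sufficient for the deep-learning part is unsupported for comparing arms, because windows and augmented copies add no independent units, and section 3.5.2 itself says an individual-level split needs more people

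*Protocol article*

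**What the plan says.** Section 3.1.1 (Inclusion criteria) gives two reasons for the sample size. The first is a pilot rule of thumb of 10 to 12 per group. The second concerns the AI analyses: "a substantial amount of data can be generated through windowing and data augmentation", transfer learning can be used, and so "it is assumed that a dataset from 36 participants will be sufficient".

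Section 3.5.2 (Methods for deep learning) supplies the count: "If we divide 330 min of recordings into 10-s segments, 1980 time series or representative images will be processed for each measurement". It continues: "In addition, the dataset can be expanded using the data augmentation technique", and concludes: "Data from 36 subjects would be sufficient in this case". On how the windows are then divided, it states that "70% will be used for training the neural network, 15% for validation, and 15% for testing". The next sentence reads: "To ensure that the training and test sets are created on an individual basis, we would need a larger number of participants", and this is left to future studies. Section 5 (Limitations) again expects 36 to be enough with transfer learning.

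Section 3.4.2 (ECG, EDR, and fNIRS data) gives the classifier an inferential purpose. It is to characterise differences between control and treatment groups, and before and after treatment, "and to show that the difference is significant". Section 3.5.3 (Performance metrics) lists accuracy, sensitivity, specificity, precision and F1, averaged over five-fold cross-validation. It does not say whether the items counted are windows or people.

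**The concern.** Section 3 (Methods/design) assigns participants, not windows, to groups in order of enrolment. Every window from a person therefore carries the same arm label. Cutting a recording into 1,980 pieces describes that person more finely, and augmenting the pieces describes nobody new. Neither adds a unit to the comparison between arms, so the volume argument does not bear on whether 36 people can support a statement about arms.

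Section 3.5.2 calls 36 sufficient and, two sentences later, says that separating training and test data by individual would need more participants. For an arm contrast, the individual-level evaluation is the one that counts, so the section undercuts its own conclusion.

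At stake is the claim of a significant arm difference in section 3.4.2. With many correlated windows per person, chance differences between 10 to 12 people per arm can look decisive.

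**Working it through.** **Inputs.** From the article: 330 min of measurement per participant, 10-s windows, 36 participants, a 15% test share, and 10 to 12 participants per group. The article gives no ICC and names no test for the classification. I assume an ICC of 0.01 to 0.5 for windows within a person.

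**1. The article's own figure.** 330 × 60 / 10 = 1,980 windows per participant per measurement, which reproduces exactly. For 36 people, 36 × 1,980 = 71,280. The 15% test share is 0.15 × 71,280 = 10,692 windows, or 297 per person if spread evenly.

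**2. What the windows are worth for an arm contrast.** Design effect DE = 1 + (m − 1) × ICC; effective number = 36m / DE. With all windows, m = 1,980:

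| Assumed ICC | DE | Effective number, of 71,280 | Factor by which the SE is understated (√DE) |
|---|---|---|---|
| 0.01 | 20.8 | 3,429 | 4.6 |
| 0.05 | 100 | 713 | 10 |
| 0.10 | 199 | 358 | 14 |
| 0.50 | 990 | 72 | 31 |

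**3. Illustrative error rate.** Suppose a nominal two-sided 5% test of an arm difference took windows as the unit. Its true error is 2 × [1 − Φ(1.96 / √DE)].

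- All windows (m = 1,980): √DE = 4.56, 10.0 and 31.5 at ICC 0.01, 0.05 and 0.5, giving 67%, 84% and 95%.
- The 15% test share (m = 297): DE = 3.96, 15.8 and 149, giving 32%, 62% and 87%.

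The number of people per arm cancels from this large-sample formula. In simulations with 12 per arm, the window-level rates were 67%, 84% and 96% for all windows and 32%, 64% and 87% for the test share. A test on participant means stayed at 4.3% to 5.4%.

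**4. Precision with the participant as the unit.** The 95% half-width for an accuracy of 0.70 is 1.96 × √(0.7 × 0.3 / n).

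- n = 10,692 windows taken as independent: ±0.9 points.
- n = 36, each person tested once by cross-validation: ±15 points.
- n = 5 or 6, since 15% of 36 is 5.4: ±40 or ±37 points.

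**5. Effect of the split.** I used a null simulation with no arm effect: 24 people in two groups, 20 features, 5-nearest-neighbour classifier. At ICC 0.2, 0.3 and 0.5, with 200 windows per person, a random split of windows gave window accuracy of 0.68, 0.79 and 0.96. A split by participant stayed near 0.50. With 100 windows per person and the random split kept, collapsing predictions to one per person raised the apparent accuracy to about 0.85, 0.97 and 1.00. Collapsing alone therefore makes a null result look stronger; the split must change first.

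**The case against.** The case on the other side has real weight.

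- **The article never calls windows independent.** It says that sufficiency is assumed, and it relies on transfer learning as well. Windows do supply training examples, and fitting a network to 36 people's recordings is feasible. This stands. A reader might infer that the sufficiency statement is simply false, or that windows are declared independent; the text supports neither. What lacks support is the step from enough data to train a network to enough people to compare arms.
- **No window-level test is specified.** This also stands. A reader might infer that the planned analysis has an error rate of 84%. The article names no such test, that figure needs an assumed ICC of 0.05 and all windows, and section 3.4.1 classifies data from mental stress only, so m would be smaller there. The rates in the working show the direction and possible size of the problem; they do not describe a planned procedure.
- **Analysis detail may sit in the statistical analysis plan.** True of clustering adjustments and of the choice of test. The point here rests on statements in the article: adequacy at 36, and the concession about an individual-level split.
- **This is a pilot and the AI part is not primary.** Section 3.5.1 assigns RMSSD, HF and LF to a mixed model or ANCOVA for pilot estimation, and section 5 calls the study preliminary. That limits the consequence. The significance aim in section 3.4.2 carries no such limit.
- **Before/after contrasts differ.** Each person contributes both labels, so the error rates above do not apply to them, although windows within a session remain correlated.

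**Conclusion.** The concern holds for between-arm inference. Sections 3.1.1, 3.5.2 and 5 present 36 participants as adequate on grounds that add no independent units to an arm comparison, and section 3.5.2 contradicts that adequacy for individual-level evaluation. The aim of showing by classification that the arm difference is significant is therefore not supported.

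The size depends on an ICC that the documents do not give. Over the assumed 0.01 to 0.5, the 71,280 windows are worth between about 3,429 and 72 independent ones for an arm contrast. The illustrative error of a window-level test is far above 5% throughout that range. The primary analysis is untouched.

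**What to change.** **Adequacy (sections 3.1.1, 3.5.2 and 5).** State that windowing, augmentation and transfer learning help to fit a network, but that the independent units for an arm comparison are the participants. Call the classification results exploratory.

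**Evaluation (sections 3.4.2, 3.5.2 and 3.5.3).**

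1. Split and cross-validate by participant, with all windows of a person in one fold and augmentation only inside training folds.
2. Then collapse predictions to one per participant before computing the Table 2 metrics for arm contrasts, and give intervals by resampling participants.
3. Either drop the word significant, or base it on permuting arm labels between participants with the model refitted each time. Note that chronological, non-random allocation makes exchangeability an assumption. For before/after contrasts, swap labels within participants.

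**Cost.** Changes to wording and analysis code, plus the computing time for refitting. No new data or participants are needed, which matters because section 3 reports data collection as completed by 30 June 2025. The price is wider intervals, probably lower reported accuracy, and a less favourable statement of adequacy.
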